### Sampling and two-stage cluster randomization

Our study will employ a cluster randomized controlled trial (cRCT) design, with public housing estates as the units of randomization. A cRCT was selected because the community-level intervention is delivered at the cluster-level and is likely to influence social interactions among residents within the same estate, making individual randomization impractical and increasing the risk of contamination. All individuals within each cluster will receive the same intervention, outcomes will be measured at the individual level, and analyses will account for clustering effects (49).

A two-stage cluster-random sampling approach will be used. In the first stage, 32 clusters will be randomly selected from the 260 public rental housing estates across Hong Kong and assigned to one of the four intervention arms by an independent researcher using 
*Random.org*
. The number of clusters may be adjusted if recruitment feasibility or cluster sizes vary. To minimize contamination, public rental housing estates assigned to different study arms will be geographically separated by at least 5 km, with a reasonable walking time of approximately 30 min or more. Figure 3 illustrates several estates located at least 5 km away from Oi Man estate, situated in the Kowloon City District. These estates include Tsz Hong Estate and Choi Wan II Estate in Wong Tai Sin District, as well as Wan Hon Estate in Kwun Tong District, with a walking time of at least 85 min. This spatial separation strategy is designed to reduce interaction between participants from different intervention arms, thereby maintaining the integrity of our intervention effects. In the second-stage, public rental housing units within each selected estate will be randomly sampled, and eligible residents will be invited to participate. This two-stage approach ensures an unbiased representation of older adults within each estates, while accounting for variation in cluster size.

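### The random draw and assignment described for the estates would almost never give the promised 5 km separation between arms, and no step builds the distance rule into the randomisation

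*Protocol article*

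**What the plan says.** All of this stands in one section of the protocol article, Sampling and two-stage cluster randomization.

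- Selection: "32 clusters will be randomly selected from the 260 public rental housing estates across Hong Kong".
- Assignment: the selected estates are "assigned to one of the four intervention arms by an independent researcher using" Random.org.
- Separation: estates placed in different arms are to be "separated by at least 5 km, with a reasonable walking time of approximately 30 min or more".
- Example: a map shows "several estates located at least 5 km away from Oi Man estate", and the text describes these estates as lying "with a walking time of at least 85 min".

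The one flexibility stated is that the number of clusters may change for recruitment feasibility or cluster size. Distance is not mentioned there. The section gives no order of operations, redraw rule, geographic blocking or constrained randomisation that would tie the separation to the draw.

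**The concern.** The section states a mechanism (random selection, then random assignment) and a property of the result (a minimum distance between arms). The mechanism as described does not deliver the property.

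The section gives contamination between residents as a reason for randomising estates, and the spacing rule is the protection against contamination between arms. If the rule is not enforced, that protection is not the one reported. If it is enforced after the arms are known, without a pre-set procedure, someone has to choose which estates to move or replace, and the allocation is open to discretion. If neighbouring estates are kept together in one arm, the units that are really randomised are groups of estates. There are then fewer of them than 32, and an analysis that counts 32 independent clusters overstates the information.

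A smaller matter is that two thresholds are given and the reader cannot tell which one decides whether a pair is acceptable.

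**Working it through.** **Inputs from the article.** 32 estates from a frame of 260; four arms of equal size (336 participants each); 5 km and about 30 minutes as minimum separation; at least 85 minutes in the example.

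**Assumptions not in the article.** 32/4 = 8 estates per arm; estates spread uniformly over a square of 250 to 10,000 km²; and, as a variant, estates clustered around 18 district centres (SD 1.5 km).

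**1. The two thresholds.** 5 km in 30 min is 5/0.5 = 10 km/h, which is not a walking pace. The example gives 5/(85/60) = 3.53 km/h; at that pace 30 min covers 3.53 × 0.5 = 1.76 km. The times differ by 85/30 = 2.83. At assumed speeds of 3 to 6 km/h, 5 km takes 100 to 50 min. Any pair that meets 5 km therefore meets 30 min automatically, and the time limit never binds.

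**2. Pairs that must comply.** All pairs: 32 × 31/2 = 496. Within-arm pairs: 4 × (8 × 7/2) = 112. Cross-arm pairs: 496 − 112 = 384.

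**3. Unrestricted draw and assignment.** 32 uniform points, random 8/8/8/8 assignment, 4,000 draws per area. The last column asks a different question: for the estates drawn, does any 8/8/8/8 allocation meet the rule?

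| Area (km²) | Mean cross-arm pairs under 5 km | Draws with none | Some compliant allocation exists |
|---|---|---|---|
| 250 | 90 | 0% | 0% |
| 500 | 49 | 0% | 0.05% |
| 1,000 | 26 | 0% | 29% |
| 1,500 | 18 | 0% | 76% |
| 2,500 | 11 | 0% | 98% |
| 5,000 | 5.7 | 0.15% | 99.9% |
| 10,000 | 2.9 | 4.9% | 100% |

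Check on the means, ignoring edges: 384 × π × 5²/area = 384 × 78.5/1,000 = 30 at 1,000 km² and 6.0 at 5,000 km². Both lie slightly above the simulated means, as expected when edges are ignored. Independent re-runs at 5,000 km² gave at most 0.4% compliant draws.

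In the clustered layout (2,000 draws per area), 0 draws complied at 1,000, 1,500 and 2,500 km². Some compliant allocation existed in 10%, 36% and 69% of draws.

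**4. A check that needs no area.** Let q be the share of estate pairs under 5 km apart. Treating pairs as independent (an approximation), the chance that all 384 comply is (1 − q)^384. For q = 1% this is 2.1%, and for q = 2% it is 0.04%. A q of 1% means that each estate has on average only 259 × 0.01 = 2.6 of the other 259 within 5 km.

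**5. Keeping neighbours in one arm.** Linking estates under 5 km apart leaves about 1, 5, 11 and 18 separately assignable groups at 300, 600, 1,100 and 2,000 km² (uniform placement), in place of 32.

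**The case against.** The strongest reply is that the section does not call the draw unrestricted. It names a random selection, an independent researcher and a tool, and then states a distance constraint. Read together, these could describe restricted randomisation, with the detail held in the full protocol. The table supports part of this: at larger assumed areas many random draws do admit a compliant allocation.

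This limits the point but does not remove it. The article reports both the mechanism and the result. A reader who follows the mechanism as written will not obtain the result, and the stated flexibility covers cluster number only. The example does not help, because it gives distances from a single reference estate and none among the other estates.

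A reader might infer three stronger things that the article does not support:

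- That the rule is impossible to meet. The article gives no coordinates and the map was not available to me, so feasibility depends on assumed areas and layouts.
- That 5 km and 30 minutes contradict each other. Both are minimums, and the 85-minute example satisfies both. The shorter limit is redundant and leaves the governing threshold unclear.
- That assignments must be changed by hand. A pre-specified constrained scheme could enforce the rule while keeping allocation random, and the article places randomisation with an independent researcher and conceals allocation until assignment. Discretionary change is a risk left open, not a stated or necessary step.

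**Conclusion.** The point holds as a gap between a stated procedure and a stated property. Unrestricted selection and assignment would almost never put all 384 cross-arm pairs at least 5 km apart: 0 of 4,000 draws at each assumed area from 250 to 2,500 km², under 1% at 5,000 km², and about 5% at 10,000 km².

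The exact figures rest on an equal split of 8 estates per arm, uniform placement and an assumed area. The conclusion does not depend on which area in that range is chosen, and the clustered layout gave the same answer at the three areas tried. The counts of linked groups illustrate the direction of the effect under uniform placement and are not properties of this trial.

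The threshold issue is one of clarity: the 30-minute figure does no work beside 5 km and should not stand next to it without a statement of which governs.

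**What to change.** Before any assignment, compute the distance matrix for the 260 estates and write the restriction into the randomisation by one of these routes:

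- Constrained randomisation: draw at random from the set of allocations that meet the cross-arm distance.
- Randomise groups of neighbouring estates as units, and analyse at that level.
- Select estates in random order subject to the distance, then assign them without restriction.

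Allow no changes after assignment. State one governing distance and delete the other figure. Confirm on the real map that this distance allows the planned number of clusters and a sufficiently large set of acceptable allocations. If 5 km is not feasible for 32 estates, report the separation actually achieved.

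The third route needs care if it spaces all selected estates, because that is stricter than the article's cross-arm rule. With 260 uniform points and 5 km between all accepted estates, 32 were reached in 0% of runs at 300 and 600 km² and in 3.5% to 6% at 1,100 km². I would not simply substitute the roughly 1.8 km implied by a 30-minute walk: that pace is inferred from one example, and the shorter distance weakens the protection against contamination.

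The cost is one-off mapping work and revised wording before assignment. Estates in dense districts may have a lower chance of selection, and the trial may have to report a shorter separation or fewer independent units than 32.

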**Figure 3 fig3:**
[figure not shown]
Map from GeoInfo Map (https://www.map.gov.hk/gm/), Lands Department, The Government of the Hong Kong Special Administrative Region.

### Sample size estimation

Based on a previous cluster randomized controlled trial designed to detect a difference between control and intervention groups for a continuous outcome (i.e., UCLA Loneliness Scale), an estimated variance was calculated at a two-tailed 5% level of significance, power of 95%, targeting a 0.087 unit difference on the UCLA Loneliness Scale while maintaining a relative precision of ±3.0% (49–52). Taking into account a 15% attrition rate across 24 months (53), unequal cluster sizes, intervention non-adherence, and potential ICC variability of *ρ* = 0.028, an effective sample size of 1,344 participants will be required, with 336 participants in each arm.

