### Measures

All outcome measures are locally validated and have been selected to capture the primary outcome, secondary outcomes and potential mechanisms of change. All outcome assessments will be conducted face-to-face at the participant’s preferred time and location across baseline (T0), as well as at 2 months (T1), 4 months (T2), and 6 months (T3) from baseline, and at 12 months (T4) and 24 months (T5) after the completion of the intervention. To minimize participant burden, outcome measures are prioritized and staggered across timepoints (see Table 2). All assessments will be administered by experienced, independent interviewers blinded to intervention allocation. All interviewers will undergo rigorous training involving comprehensive familiarization with the measurement tools, clinical vignettes, and on-site practice to achieve and maintain high inter-rater and intra-rater reliability (ICC >0.9) throughout the study.

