#### Primary outcome

Loneliness will be assessed by the 20-item Revised UCLA Loneliness Scale (UCLA-LS) (59, 60), where participants will rate each item based on the frequency they experience feelings of loneliness, using a 4-point Likert scale ranging from 1 = Never to 4 = Always. Total scores range from 20 to 80, with higher scores indicating greater levels of loneliness.

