### Planned statistical analysis

Descriptive statistics will be used to summarize baseline characteristics of the participants within each arm. An intention-to-treat approach will be adopted. Missing values will not be replaced because mixed-effects models can accommodate participants with at least one outcome measurement under the assumption that data are missing at random. All analyses will be appropriately accounted for the cluster randomized controlled trial (cRCT) design, recognizing that participants are nested within clusters and outcomes within clusters may be correlated. To assess intervention effects of different arms on primary and secondary outcomes, generalized linear mixed models (GLMM) with random intercepts for clusters, fixed effects for time points (i.e., T0, T1, T2, T3, T4, T5), group (using the control group as the reference), and their interaction terms will be utilized. In addition to GLMM, generalized estimating equations (GEE) with robust standard errors and an exchangeable working correlation structure will be used for sensitivity analysis, with small sample corrections applied as needed to control the rate of type I error. To ensure robustness, results from GLMM and GEE approaches will be compared, with multiple testing corrections such as Bonferroni adjustments applied as appropriate. Sensitivity analyses will include per-protocol and complete case approaches to evaluate the influence of adherence and missing data. Mediation analyses of psychosocial and other potential mediators will employ multilevel modelling techniques suited for clustered data. Statistical significance was defined as *p* < 0.05. All statistical modelling will be conducted using SPSS version 29.0, which provides robust tools for multilevel mixed-effects modelling including GLMM and GEE, with options for controlling cluster effects and covariate adjustment.

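### The stated 95% power for a 0.087-unit UCLA difference cannot hold together with 336 per arm, ICC 0.028 and a 20 to 80 total score

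*Protocol article*

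**What the plan says.** All of the design figures stand in one paragraph, Sample size estimation. It sets a two-sided 5% level and "power of 95%, targeting a 0.087 unit difference on the UCLA Loneliness Scale", adds a relative precision target of ±3.0%, and allows for 15% attrition over 24 months, unequal cluster sizes, non-adherence and an ICC of 0.028. It concludes that "an effective sample size of 1,344 participants will be required, with 336 participants in each arm". It says that "an estimated variance was calculated" but gives neither a variance nor an SD, and it does not say on which metric 0.087 is measured.

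Two other sections matter. Primary outcome defines the 20-item Revised UCLA scale as a total: "Total scores range from 20 to 80, with higher scores indicating greater levels of loneliness". Sampling and two-stage cluster randomization gives 32 estates for four arms, which is 8 per arm if split equally, and notes that the number may be adjusted.

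**The concern.** On a 20 to 80 total, 0.087 is less than a tenth of a point, while any one participant's score moves in whole points. If 0.087 is instead a standardised effect, it is very small, and a few hundred clustered participants per arm would not normally detect it. Either way, the printed difference, power, ICC, attrition and sample size look incompatible.

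Power and target difference are headline figures of the trial. As printed, the paragraph does not tell a reader what size of effect the trial can detect, and its 95% claim cannot be checked or relied on.

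**Working it through.** **Inputs from the article.** Two-sided alpha 0.05 (z = 1.960); power 95% (z = 1.645); difference 0.087; ICC 0.028; attrition 15%; 336 per arm; 32 estates, so 8 per arm if split equally.

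**Assumed.** The SD. I use 5 to 12 points on the 20 to 80 total, and 1 for the standardised reading.

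**Step 1: what an arm is worth.**
- Analysed per arm: 336 × 0.85 = 285.6
- Analysed per estate: 285.6 / 8 = 35.7
- Design effect: 1 + (35.7 − 1) × 0.028 = 1.972
- Effective number per arm: 285.6 / 1.972 = 144.9 (about 580 over four arms)

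**Step 2: trying to reproduce the plan's figure.** For a standardised difference of 0.087, the number per arm before clustering is 2 × (1.960 + 1.645)² / 0.087² = 3,434, about ten times 336. On the raw total, with SD 8 to 10, it is about 220,000 to 343,000 per arm. Other routes also fail to give 95% power or 336 per arm: a one-sided test, pooling the three active arms, treating 672 or 1,344 as the number per arm, reading 0.087 as Cohen's f, and reading it as a difference in proportions. For the standardised reading, so does adjustment for baseline at correlations of 0.3 to 0.7.

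**Step 3: power for 0.087 on three readings.** The standard error of the standardised difference is √(2 / 144.9) = 0.1175. Power is taken from the normal approximation at (difference / SD) / 0.1175.

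| Reading of 0.087 | Assumed SD (total score) | Standardised difference | Power |
|---|---|---|---|
| Points on the total | 5 | 0.0174 | 5.3% |
| Points on the total | 12 | 0.0073 | 5.0% |
| Standardised effect | not needed | 0.087 | 11.5% (10.6% with t on 14 df) |
| Item mean: 20 × 0.087 = 1.74 points | 5 | 0.348 | 84% (79% with t on 14 df) |
| Item mean: 1.74 points | 8 | 0.2175 | 46% |
| Item mean: 1.74 points | 10 | 0.174 | 32% |

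**Step 4: dependence on the number of estates.** Take all 336 in each arm as independent, with no clustering and no loss. Power is then 5 to 6% for points on the total (SD 5 to 12) and 20% for the standardised reading. Changing the number of estates therefore cannot rescue either reading.

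**Step 5: what the design detects.** (1.960 + 1.645) × 0.1175 = 0.424 SD at 95% power. A t reference on 28 df (32 estates less 4 arms) gives 0.44 SD, and 14 df (16 estates less 2 arms) gives 0.46 SD. In points, 0.424 SD is 3.4 at SD 8 and 4.2 at SD 10.

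**Step 6: the SD that would make the claim true.** For points on the total, 0.087 / 0.424 = 0.21 points. With no clustering or attrition it is 0.31 points. Neither is credible for a whole-number score from 20 to 80. For the item-mean reading, 1.74 / 0.424 = 4.1 points.

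**The case against.** The strongest reply is that the SD and the metric are unstated and rest on cited sources not shown here, so no single power figure can be called the actual one. That stands. It matters most for the item-mean reading: at SD 5, an assumed baseline correlation of 0.6 would lift power from 84% to about 96%. But this needs a metric that Primary outcome does not define, an SD at the low end of the assumed range and an efficiency gain that the sample size paragraph does not mention. It shows that 0.087 might have a coherent origin, not that the text is right as printed.

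A second reply is that 0.42 SD should not simply be written in as the new target. That also stands. The figure describes one unadjusted comparison. It leaves out the unequal cluster sizes and non-adherence that the paragraph itself lists, both of which would worsen it. It also leaves out any gain from the baseline measure, which at assumed correlations of 0.5 to 0.7 would bring it to about 0.37 to 0.30 SD.

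A reader might be tempted to add further faults, which the article does not support:
- Sizing at 5% is not an error because of "multiple testing corrections such as Bonferroni adjustments applied as appropriate"; the final multiplicity scheme is commonly left to the analysis plan.
- The last visits are "at 12 months (T4) and 24 months (T5) after the completion of the intervention", so the 24-month attrition figure may refer to that follow-up. Extending the loss to 30 months at a constant rate (about 18%) moves the detectable difference only from 0.424 to 0.428 SD.
- The article gives no expected effect for any contrast, so it cannot be said that the incremental contrasts will show smaller effects.
- A null result would be judged by its confidence interval, so it need not be misread as excluding tiny effects.

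**Conclusion.** The power statement is wrong as written. With the article's own inputs and 8 estates per arm, power for 0.087 is about 5% as points on the 20 to 80 total and about 11% as a standardised difference. The first rests on an assumed SD of 5 to 12 but hardly varies across that range; the second needs no SD in points. Neither conclusion depends on the estate count. Only an item-mean reading comes near the claim, and there an unadjusted comparison needs a total-score SD of about 4.

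A reader might infer that the trial has only 5% power, or that it is too small. The article does not support that. The 5% and 11% refer to the printed difference of 0.087, whereas the same design has 95% power for a moderate difference of roughly 0.42 to 0.46 SD, subject to the allowances not yet included. What fails is the stated pairing of target and power.

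**What to change.** Rewrite the sample size paragraph as follows.
- State the metric of 0.087 (points on the total, item mean or standardised) and the SD used, with its source.
- Recompute, and replace the power or target-difference statement with what 336 per arm in the planned estates delivers, in points on the 20 to 80 scale.
- Show the number of estates per arm, the design effect, and the allowances for attrition, unequal cluster size and non-adherence. If baseline adjustment is relied on, state the assumed correlation.
- Call 1,344 the enrolled number. After 15% attrition and the design effect, the effective number is about 580.
- Remove the ±3.0% precision clause, or explain what it refers to and how it entered the calculation.

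The 0.42 SD figure above is a check on the recomputation, not a replacement target. Whether the recomputed difference is worth detecting is for the sponsor to justify.

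The cost is one recalculation and one reworded paragraph. The correction itself adds no participants. The downside is that the stated detectable difference becomes less favourable.

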### Participants

The inclusion criteria are (i) Chinese older adults aged 65 years and older residing in a public housing estate, (ii) ability to complete the intervention in Cantonese, (iii) living in poverty, defined by self-reported material deprivation, operationalized as the inability to afford at least 5 items on the material deprivation index (54), and (iv) experiencing loneliness, defined as a score of ≥6 on the 3-item UCLA Loneliness scale (55). The exclusion criteria include (i) diagnosed with cognitive impairment, psychiatric disorder, learning disability, or suicidal ideation, and (ii) actively engaged in psychotherapy or psychosocial intervention in the past year.

### Allocation concealment and blinding

Randomization will be conducted by an independent researcher, and allocation will remain concealed from other researchers and participants until assignment. Outcome assessors will be blinded to participants’ intervention allocation. Participants will be partially unblinded, as they are aware of the intervention they receive, but they will be blinded to study hypotheses. Interventionists will be unblinded due to the nature of the interventions. To further reduce contamination, participants will be asked not to discuss the intervention with residents from other estates during the study period.

